## Abstract

**Objective:**

A growing body of evidence suggests patients with late‐onset seizures are at an increased risk of stroke, but the potential for reducing cardiovascular morbidity through risk factor screening and management is unknown. We aim to determine whether individuals with new‐onset unprovoked seizures after middle age should undergo vascular risk assessment. The long follow‐up needed to assess stroke risk and the known benefit of vascular risk factor modification make a standard RCT logistically and ethically challenging. Instead, we propose and have developed a protocol for a cluster project assessing the effect of vascular risk factor screening in an intervention trial as well as a cohort study.

**Methods:**

Participating neurology clinics will implement standard cardiovascular risk factor assessment into the routine evaluation for individuals aged ≥50 years attending their first specialized consultation after an unprovoked seizure, excluding those with progressive brain disease. The project has two interlinked components: a prospective single group trial, in which risk factor assessment is performed and subsequent management is followed for one year; and a register‐based cohort study examining the long‐term effects of the intervention on a system level by comparing patients attending initial consultations in the 2 years after start of the study, with patients seen in the four preceding years at the same clinics.

**Analysis:**

The primary outcome of the intervention trial is the proportion of patients receiving subsequent pharmacological treatment. The primary outcome of the cohort study is the incidence of acute stroke in the Swedish Stroke Register.

**Ethics and Dissemination:**

Swedish Ethical Review Authority approval (which is valid for 2 years only) will be sought when funding is obtained. The results will be disseminated through peer‐reviewed scientific publications.

**Registration Details:**

The study will be registered at clinicaltrials.gov.

**Plain Language Summary:**

A first seizure in a middle‐aged or older person indicates a higher risk of stroke. It is not known whether investigating and treating blood pressure, blood cholesterol, or similar risk factors after a first seizure is an effective way to prevent stroke. A traditional clinical study would need too many patients and it would be unethical not to treat the control group. We have designed a study in which participating neurology departments change their practice to test and treat vascular risk factors. Patients are then compared to historic controls using registered data.

Key points
The proposed study investigates whether standardized vascular risk factor assessment is warranted in patients with late‐onset seizures.The study has a short‐term analysis of proportion receiving therapy after the intervention.The study has a long‐term analysis of stroke risk compared to historic controls.Swedish comprehensive registers are used for the long‐term outcome, minimizing loss to follow‐up.A limitation is the non‐randomized design, but untreated controls are unethical given the benefits of vascular risk factor modification.

## INTRODUCTION

1

### Background

1.1

Cerebrovascular disease is the most common cause of epilepsy after middle age. Interestingly, seizures can also precede stroke.^1^, ^2^, ^3^, ^4^, ^5^ UK primary care data indicated a nearly threefold increased risk of stroke after a first seizure in those aged ≥60 years,^4^ a finding that was recently replicated in Swedish population wide register data, albeit with a slightly lower risk (HR 2.27, 95%CI: 1.87–2.75).^1^ The relative increase in risk was greater for intracerebral hemorrhage (HR 2.51, 95%CI: 2.08–3.04) than ischemic stroke (HR 1.68, 95%CI: 1.56–1.80).^1^ Vascular risk factors increase the risk of late‐onset epilepsy,^6^ so a plausible explanation is that late‐onset seizures reflect occult cerebrovascular disease that has not yet resulted in a clinical stroke. This notion is further supported by a higher prevalence of silent cerebrovascular disease on imaging in patients with late‐onset seizures than in healthy controls.^7^ The highest increase in stroke risk is seen in the first year following the first seizure.^1^ Another contributing factor could be detrimental effects of antiseizure medications (ASM) on vascular risk prevention, like interactions with lipid‐lowering drugs.^8^

Given the emerging evidence of increased stroke risk after late‐onset seizures, the potential benefits of vascular risk factor management in such patients are being discussed,^7^, ^9^ but evidence on the optimal nature and effect of these interventions is lacking. In addition to stroke, other cardiac events like arrythmias or sudden cardiac death are associated with epilepsy or ictogenic mechanisms^10^, ^11^ but whether vascular risk factor intervention mitigates such risks is unknown. Current clinical practice does not consider vascular risk factors in management of first seizures. It is simply not known whether detection and treatment of hypertension and/or optimization of serum lipids is beneficial or not in this patient group.

### Rationale

1.2

Since there can be a long latency between a first seizure and stroke, and since benefits of treatment of many vascular risk factors are well established, a standard RCT is logistically and ethically challenging. Swedish comprehensive health registers allow a multicenter register‐based randomized controlled trial (RRCT) design, but even with the advantages of that approach recruitment would be challenging. A 1:1 randomized study that assumes a 10‐year cumulative stroke rate of 10% and a 30% relative risk reduction from the intervention would require 247 events and 4494 participants to be completed in 5 years (*α* = 0.05; *β* = 0.2; censoring rate = 0.1). Since all potentially recruitable cases in Sweden are roughly 2000 candidates per year (incidence of late‐onset seizures: ~60 per 100 000), this is not a feasible study design. Furthermore, the benefits of treatment of hypertension and diabetes as well as smoking cessation are well known, making it ethically dubious to withhold such interventions from a control group. Since the research question is not whether vascular risk factor assessment is beneficial, but whether vascular risk assessment specifically in the work‐up of late‐onset seizures is beneficial on a system level, we decided on a cluster‐based design.

### Objectives

1.3

This project aims to assess the impact of implementing vascular risk factor assessment (screening) in the work‐up of individuals with a new‐onset unprovoked seizure after age 50. The vascular risk assessment equals the opportunistic screening that can already be done during health visits according to Swedish guidelines. Any vascular risk factor modification after the assessment is done according to existing guidelines. We aim to assess both the proportion of patients that receive pharmacotherapy as a result of the assessment and the effect on long‐term stroke risk.

## METHODS AND ANALYSIS

2

### Study design

2.1

Participating neurology clinics in Sweden will introduce cardiovascular work‐up as the standard of care following late‐onset seizures. Subsequently, we will use pseudonymized data from comprehensive national registers to compare outcome differences between new patients (those attending first visits) before and after the practice change. In addition, following the new standard of care implementation, all eligible patients are offered to participate in a one‐year prospective trial that examines the prevalence of modifiable vascular risk factors and subsequent cardiovascular treatment (Figure 1).

**FIGURE 1 epi412987-fig-0001:**
[figure not shown]
The study design comprises two main components: (A) a prospective single group trial with a one‐year follow‐up assessing the prevalence of vascular risk factors and the impact of screening on subsequent management and (B) a register‐based cohort study examining the long‐term effect on vascular risk by comparing patients seen after introduction of the new standard to historical controls from the same sites.

### Intervention: Evaluating modifiable vascular risk factors

2.2

The evaluation of vascular risk factors aims to identify and manage modifiable vascular risk factors early, in line with the current ESC guidelines on cardiovascular disease prevention.^12^ Like most work‐up protocols, investigators may refrain from evaluating selected cases when such intervention is deemed inappropriate or the benefit of potential cardiovascular prevention is minimal. To promote adherence to the practice change, relevant health care staff will receive information during a 6‐month “briefing and implementation phase,” during which they can also report barriers to adherence and suggest site‐specific logistical improvements.

The examinations included in the work‐up are at the investigator's discretion to align with existing local guidelines; however, the minimum requirements are listed in Table 1. A registered nurse or a nursing associate will generally be available with each initial consultation to conduct any ordered examinations, minimizing the need for additional visits. Using composite risk assessment tools, for example, SCORE2/SCORE2‐OP, is advised to guide preventive measures in individuals without already established cardiovascular disease. Investigators are free to give lifestyle advice and prescribe medications according to local or international guidelines and to tailor treatment according to the patient's preferences; the study protocol does not specify any management strategies for identified conditions beyond what existing Swedish guidelines already recommend. Participating sites will have regular education on what the guidelines stipulate regarding blood pressure targets, lipid level targets, and smoking cessation.

**TABLE 1 epi412987-tbl-0001:** Mandatory components of the vascular risk factor evaluation.

Procedure
Family history of vascular disease
Tests/examinations (order or obtain from medical records [past 3 months])
Weight
Height
Waist circumference
12‐lead ECG
Resting and standing blood pressure
Total cholesterol
HDL cholesterol
LDL cholesterol
HbA1c
High sensitivity CRP
Serum creatinine
Urine albumin‐to‐creatinine ratio
Medical history
Atherosclerotic cardiovascular disease
Atrial fibrillation
Congestive heart failure
Diabetes mellitus
Hypertension
Kidney disease
Life‐style risk factors (smoking, exercise)

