### Sample selection

2.3

Patients undergoing their first‐ever specialized assessment for unprovoked seizures or epilepsy with onset after age 50, who also receive a vascular risk factor evaluation (minimum requirements are outlined in Table 1) in conjunction with their initial consultation (within 1 month), are invited to participate in a prospective one‐year trial. Individuals unable to provide informed consent and those with established progressive brain disease, that is, brain tumor or neurocognitive disorder, will be excluded. Notably, we will not exclude patients already on primary or secondary cardiovascular prevention; thus, the study will include groups for whom the benefit from the intervention may be limited.

In addition, we will conduct a system‐level register‐based cohort study based on data from the National Patient Register (NPR), which covers information on all specialized health care encounters in Sweden, and the Swedish Prescribed Drug Register (SPDR), which encompasses details of all prescribed drugs dispensed at pharmacies. Patients aged ≥50 with a first‐ever outpatient appointment to one of the participating clinics and a first‐listed diagnostic code for seizures or epilepsy (ICD‐10: R568, G40) are included. Exclusion criteria will be (i) preexisting seizures/epilepsy, as demonstrated by a registered diagnostic code for seizures (ICD‐10: R568, G40, G41) or a dispensed antiseizure medication (ATC‐code: N03) more than 3 months before the initial consultation, (ii) a registered diagnostic code for stroke or TIA (ICD‐10: I61, I63, I64, or G45 except G454) before the initial consultation, or (iii) progressive brain disease, as indicated by diagnostic codes or drug prescriptions suggestive of brain tumors (ICD‐10: C71, D33, D43, C793) or neurocognitive disorders (ICD‐10: F00‐F03, F051, G30, G318, G912; ATC code: N06D). The only difference in eligibility criteria between the intervention group and the control group will be the period of recruitment; the former will consist of patients with their initial consultation in the 2 years following the “briefing and implementation phase” of the center, whereas the control group will encompass those seen in the four preceding years at the same site.

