### Outcomes

2.4

The purpose of the prospective single group trial is to assess the prevalence of vascular risk factors and the impact of screening on subsequent management and vascular risk. The primary outcome is the proportion of cases receiving pharmacological intervention following the vascular risk factor evaluation; pharmacological intervention is defined as the initiation or dose adjustment of antihypertensive agents, antidiabetic agents (including SGLT2 inhibitors used for other indications), lipid‐lowering agents, antiplatelet agents, or anticoagulants (Table 2). Secondary outcomes are as follows: (i) proportion of cases where the screening procedure uncovers previously undetected vascular risk factors, subdivided into hypertension, diabetes mellitus, moderate‐to‐severe chronic kidney disease, and atrial fibrillation, (ii) alterations in modifiable vascular risk factors at the one‐year follow‐up compared to baseline measurements, (iii) changes in SCORE2/SCORE2‐OP risk scores at the one‐year follow‐up, specifically in individuals without established cardiovascular disease, (iv) proportion of participants with adverse effects following pharmacological intervention, (v) proportion with arrythmias or QT‐prolongation captured during admissions, and (vi) proportion of participants remaining on initiated treatment at the 12‐month follow‐up.

**TABLE 2 epi412987-tbl-0002:** Variables and outcomes for the two analyses.

Variables	Primary outcome	Secondary outcomes
One‐year single group prospective analysis		
See Table 1	% with pharmacological intervention	Hypertension, diabetes mellitus, moderate‐to‐severe chronic kidney disease, atrial fibrillation, alterations in modifiable vascular risk factors compared to baseline, changes in SCORE2/SCORE2‐OP at the one‐year follow‐up, % adverse effects
Matched cohort long‐term analysis		
Demographics, vascular disease, comorbidities that can cause seizures, medical treatments	Stroke	Major adverse cardiovascular events, all‐cause mortality, stroke severity (NIHSS at stroke admission; modified Rankin Scale 3 months post‐stroke), conduction block/arrhythmia, and occurrence of recurrent seizures

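### The single-group primary proportion is conditional on being evaluated, and evaluation may be skipped when little benefit is expected, so it probably overstates the yield of screening all eligible first visits

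*Protocol article*

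**What the plan says.** Four statements in the protocol article bear on who is counted.

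- **Section 2.2 (Intervention)** gives discretion over the evaluation itself: "investigators may refrain from evaluating selected cases when such intervention is deemed inappropriate or the benefit of potential cardiovascular prevention is minimal". The article sets no criteria for this.
- **Section 2.3 (Sample selection)** sets the entry condition for the one-year trial: patients "who also receive a vascular risk factor evaluation (minimum requirements are outlined in Table 1) in conjunction with their initial consultation (within 1 month), are" the ones invited. Further on, after stating that patients already on primary or secondary prevention are not excluded, it adds: "thus, the study will include groups for whom the benefit from the intervention may be limited".
- **Section 2.1 (Study design)** says that, once the new standard is in place, "all eligible patients are offered to participate in a one‐year prospective trial".
- **Section 2.4 (Outcomes)** defines the endpoint: "The primary outcome is the proportion of cases receiving pharmacological intervention following the vascular risk factor evaluation". Starting a drug in the listed classes or adjusting its dose both count.

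The aim in section 1.3 is to "assess the impact of implementing vascular risk factor assessment (screening) in the work‐up of individuals with a new‐onset unprovoked seizure after age 50". The abstract asks whether people with late-onset seizures should be assessed at all, and section 1.2 places the question at system level.

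**The concern.** The reason allowed for skipping is tied to the outcome. A patient in whom prevention is judged to offer little is, on that judgement, less likely than others to have a preventive drug started or adjusted. Such patients can be left unevaluated, and unevaluated patients cannot enter the trial, so the denominator is selected on a predictor of the numerator. This happens whenever consent is taken, even if consent precedes every test result.

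At stake is how the headline figure will be read. Among evaluated patients it describes what evaluation led to. Read as the yield of making assessment part of the routine work-up, which is how the project frames its question, it is probably too high. The planned confidence interval covers sampling error only, and a larger sample would not remove the shift.

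**Working it through.** **Inputs from the plan.** Section 2.6 gives an assumed proportion of 50%, a margin of error below 5 points and a minimum sample of 385. Section 2.5 gives a 95% interval by the normal approximation.

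**The plan's own figure.** n = 1.96² × p(1 − p) / d², with p = 0.50 and d = 0.05, gives 384.15 (z unrounded), rounded up to 385. The half-width at n = 385 is 1.96 × √(0.25/385) = 4.99 points. The stated sample size reproduces, and nothing below changes it.

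**Inputs not in the plan (assumptions).** Let s be the share of eligible first visits not evaluated, and r the proportion treated, or who would be treated, among them. The documents give neither. If only treatment that follows an evaluation is counted, r = 0 for skipped patients by definition. If the question is what would have happened had they been evaluated, r is unknown. It should lie below p for patients skipped because little benefit was expected. I take s from 5% to 30% and r from 0 to 25%.

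**Formula.** Proportion over all eligible first visits = (1 − s)p + s·r. Overstatement = p − [(1 − s)p + s·r] = s(p − r).

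**Overstatement in percentage points, p = 50%:**

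| s | r = 0 | r = 10% | r = 25% |
|---|---|---|---|
| 5% | 2.5 | 2.0 | 1.25 |
| 10% | 5.0 | 4.0 | 2.5 |
| 20% | 10.0 | 8.0 | 5.0 |
| 30% | 15.0 | 12.0 | 7.5 |

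For example, with s = 20% and r = 10%: 0.8 × 50% + 0.2 × 10% = 42%, which is 8 points below 50%.

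**When the shift equals the margin.** Setting s(p − r) = 5 points gives s = 0.05/(0.50 − r): 10% skipped at r = 0, 12.5% at r = 10%, and 20% at r = 25%.

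**Sensitivity to p.** At p = 30%, skipping 10% shifts the figure by 3.0, 2.0 or 0.5 points for r = 0, 10% or 25%, and skipping 20% by 6.0, 4.0 or 1.0 points.

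**When it vanishes or reverses.** The shift is zero if s = 0 or r = p. It reverses if r exceeds p: with p = 50%, r = 60% and s = 10% it is −1.0 point. For skips made because benefit is minimal, r ≥ p would contradict the reason for skipping. For skips made because evaluation is deemed inappropriate, the documents do not settle the direction.

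**The case against.** The strongest reply is that the outcome is already conditional. Section 2.4 counts treatment after the evaluation, and section 1.3 speaks of pharmacotherapy resulting from it. Among evaluated, consenting patients the skip rule causes no bias. Section 2.2 also presents the discretion as an ordinary part of the practice being introduced, and the system-level question is assigned mainly to the register cohort, which does not require evaluation. All of this stands. It means that the endpoint is not wrong as defined and that the remedy concerns labelling and a supplementary figure. It does not make the conditional proportion an answer to the broader question in the abstract and in sections 1.2 and 1.3.

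Three stronger readings may tempt a reader, and the documents do not support them.

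- *Sections 2.1, 2.2 and 2.3 contradict each other.* They are in tension only. Section 2.1 speaks of eligible patients, and section 2.3 makes evaluation part of eligibility. The remark on limited benefit concerns patients already on prevention: no criterion excludes them, though an investigator could still skip them case by case.
- *Incomplete work-ups add the same bias.* The tests in Table 1 are not independent of one another, since several are blood measurements that can be taken together, and recent results from the records are accepted. A patient who lacks one measurement may be treated about as often as anyone else.
- *The register cohort retains every skipped patient.* It excludes prior stroke or TIA, which the trial does not list as an exclusion. It also has no exclusion for inability to consent. The two populations therefore differ whatever the skip rule does.

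It is also fair to say that a screening log may sit in the full protocol, which is not shown. Its absence from a condensed article is not the point made here.

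**Conclusion.** The concern holds in a limited form. Discretionary skipping combined with entry restricted to evaluated patients makes the primary proportion a statement about evaluated, consenting patients only. For patients skipped because little benefit is expected, it probably overstates the yield over all eligible first visits.

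The direction for these skips follows from the protocol's own reason for allowing them. The size does not follow from the documents. Under the assumptions of 50% treated among the evaluated and 0-25% among the skipped, the overstatement is 2.5-5 points if 10% are skipped and 5-10 points if 20% are, against a margin of 5 points. With rare skipping it would be unimportant. The sample size of 385 is unaffected, and so is the cohort study's stroke comparison.

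**What to change.** 1. State that the primary proportion is conditional on evaluation, and limit the conclusions drawn from it to evaluated, consenting patients.
2. Add a secondary system-level proportion: new dispensing of the listed drug classes in the Swedish Prescribed Drug Register among all intervention-period first visits in the National Patient Register cohort. Set it beside the same proportion in the historical control period, so that background starts are not credited to the screening. Either tabulate before the prior stroke/TIA exclusion or state that the figure carries it. Note that dispensing data capture dose changes poorly, although dose changes count in the primary outcome.
3. Have sites count eligible first visits and how many were evaluated. The registers as described cover encounters and dispensed drugs and do not record completion of Table 1, so they cannot separate skipped patients from evaluated patients who declined consent.
4. Reconcile the wording of sections 2.1, 2.2 and 2.3 on who is offered the trial.

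The cost is wording, a small site tally and one extra tabulation from registers already planned. The headline yield will probably look less favourable. The sample size and the investigators' discretion stay as they are.

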### Data analysis plan

2.5

Descriptive statistics will be presented as median (interquartile range) or number (%). For the single group study, we will use the normal approximation method to calculate 95% confidence intervals for proportions, including the primary outcome. Comparisons between baseline and one‐year follow‐up measurements will involve paired analyses, for example, McNemar's test for categorical data and paired t‐test or a non‐parametric equivalent for continuous data, depending on the data distribution. The analyses will be stratified by age groups, sex, and previously established cardiovascular risk factors. All tests will be two‐sided and considered statistically significant at *p* < 0.05.

The cohort study examines time to the different events of interest. We will use the Kaplan–Meier method and Cox proportional hazards regression to evaluate all‐cause mortality. For other events of interest, death will be accounted for as a competing risk. Survival times are calculated from the initial consultation until either the event of interest, death or study end, whichever comes first. To compare baseline group differences, we will utilize the Fisher exact test, the *χ*
^2^ test, or the Mann–Whitney *U* test, depending on the data characteristics. We do not anticipate any significant group differences; however, we will perform univariable and multivariable regression analyses to identify and adjust for any relevant covariates (age, sex, medical history, prescriptions of drugs used for cardiovascular prevention). Subgroup analyses will comprise previously “healthy” individuals (no drug prescriptions related to cardiovascular prevention) and individuals without established cardiovascular disease (defined as not being prescribed antiplatelet agents or anticoagulants). Analyses will also be stratified by age groups and sex.

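### Baseline blood pressure may come from records of the index-seizure contact, so recovery from an acute elevation would count as one-year improvement in secondary outcomes (ii) and (iii)

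*Protocol article*

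**What the plan says.** Section 2.2, Table 1, lists the mandatory parts of the vascular risk evaluation. The measurements stand under the heading "Tests/examinations (order or obtain from medical records [past 3 months". The items below it include "Resting and standing blood pressure", lipids, HbA1c, creatinine, urine albumin and "High sensitivity CRP".

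Section 2.3 requires the evaluation to take place "in conjunction with their initial consultation (within 1 month". It sets no minimum interval from the seizure and does not say that the one-month limit narrows the three-month records window.

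Section 2.4 names secondary outcome (ii) as "alterations in modifiable vascular risk factors at the one‐year follow‐up compared to baseline measurements" and outcome (iii) as "changes in SCORE2/SCORE2‐OP risk scores at the one‐year follow‐up", the latter in people without established cardiovascular disease.

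Section 2.5 states: "Comparisons between baseline and one‐year follow‐up measurements will involve paired analyses". McNemar's test and the paired t-test (or a non-parametric equivalent) are given as examples, two-sided at 0.05. There is no control group in this component.

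**The concern.** The patients are at their first specialised assessment after a seizure. Their most recent recorded blood pressure may be the one taken when they sought care for that seizure. Table 1 allows it to serve as the value in the evaluation, and no section rules it out. The one-year value is taken long after the event. If the acute reading was temporarily raised, its return to the usual level enters the paired difference as a fall.

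The error runs towards apparent benefit, and a single-group comparison cannot separate it from an effect of screening. One stated purpose of this component (section 2.4) is to assess the impact of screening on vascular risk, so outcomes (ii) and (iii) are where a reader will look for that evidence.

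The matter is settled when data are collected. If the date and care setting of a baseline value are not captured, no later analysis plan can identify and set aside the acute ones.

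**Working it through.** **The plan's own figure.** Section 2.6 gives a minimum of 385 patients for a margin of error under 5% at a proportion of 50%. Check: n = 1.96² × 0.5 × 0.5 / 0.05² = 384.1, rounded up to 385. This reproduces and is not in dispute. It serves below as the number of pairs.

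**Can acute values enter?** Three places, side by side:
- Table 1 admits records up to three months old.
- Section 2.3 ties the evaluation to the consultation but sets no gap from the seizure.
- The register cohort's criteria in section 2.3 exclude earlier seizure codes or antiseizure drugs only when they date from "more than 3 months before the initial consultation". That rule belongs to the other component, so it is indirect evidence. It does show that the project expects care for the index seizure inside the same three-month span.

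Acute values are therefore permitted. The article does not say that they will be used.

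**Illustration of size.** The article gives none of the following, so all are assumptions: systolic SD 18 mmHg at each time point; correlation r between baseline and one year of 0.6 or 0.7; a share f of baselines from the acute contact; an elevation d in those, gone by one year; no true effect.

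SD of the paired difference = 18 × √(2(1 − r)):
- r = 0.6: 16.10 mmHg; SE = 16.10/√385 = 0.82
- r = 0.7: 13.94 mmHg; SE = 13.94/√385 = 0.71

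The smallest mean fall reaching p < 0.05 is 1.96 × SE, that is 1.6 mmHg (r = 0.6) or 1.4 mmHg (r = 0.7).

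Spurious mean fall m = f × d. Chance of p < 0.05 with no true effect = Φ(m/SE − 1.96) + Φ(−m/SE − 1.96).

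| Share f | Elevation d | Mean fall m | r = 0.6 | r = 0.7 |
|---|---|---|---|---|
| 10% | 5 mmHg | 0.5 mmHg | 9% | 11% |
| 10% | 10 mmHg | 1.0 mmHg | 23% | 29% |
| 20% | 5 mmHg | 1.0 mmHg | 23% | 29% |
| 20% | 10 mmHg | 2.0 mmHg | 68% | 80% |

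Mixing acute and ordinary baselines adds f(1 − f)d² to the variance of the difference. For f = 20% and d = 10 mmHg this is 0.2 × 0.8 × 100 = 16. The SEs become √(259.2 + 16)/√385 = 0.85 and √(194.4 + 16)/√385 = 0.74, and the chances 66% and 77%. With and without this term, the range for a 2 mmHg fall is about 66 to 80%.

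**The case against.** The strongest reply is that Table 1 is a clinical checklist and not a definition of the analysis baseline. Section 2.4 speaks only of baseline measurements, section 2.2 expects a nurse to be on hand at most consultations, and a full protocol or data-collection form may settle which value is analysed. Part of this stands: on-site measurement may turn out to be usual. But the article does state a rule for where the values come from, that rule admits acute readings, and no other baseline is named for the change outcomes.

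Several stronger readings are tempting and are not supported:

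- *The percentages estimate the trial's false-positive rate.* They do not. Every input except 385 is assumed, and at 10% of baselines 5 mmHg high the chance is 9 to 11%, not far above the nominal 5%.
- *Regression to the mean adds a further fall of 5 to 9 mmHg.* A figure of that kind applies to patients selected for a high baseline reading, such as 140 mmHg or above. Eligibility sets no pressure threshold, and the planned strata are age, sex and previously established risk factors. An unselected group has no expected mean shift from this source.
- *CRP change is distorted.* CRP is measured, but it is not a named outcome.
- *New diagnoses under outcome (i) are inflated.* This needs a rule that one acute reading is enough for hypertension or kidney disease, and the article states no such rule.
- *The whole project is affected.* The primary outcome's definition and the register cohort do not use this comparison.

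It is also fair that standing pressure, which Table 1 requires, is less likely to be found in acute records, and that the article already names the non-randomised design as a limitation. Naming that limitation does not deal with a bias built into the baseline itself.

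**Conclusion.** The concern holds in a limited form. The plan permits baseline blood pressure from the index-seizure contact and analyses one-year change without a control group, so resolution of a transient elevation would appear as improvement in outcome (ii). It would also appear in outcome (iii), because systolic pressure enters the risk score (general knowledge; the article does not list the score's inputs). The direction of the bias is clear if acute readings are raised. Its size cannot be determined from the article. Under the assumptions above, a spurious mean fall of only 1 to 2 mmHg would be declared significant in roughly a quarter to four fifths of trials with no true effect. This is an inexpensive improvement to two secondary outcomes and does not threaten the primary result of either component.

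**What to change.** 1. Keep record-derived values for the clinical work-up, as Table 1 now allows.
2. For outcomes (ii) and (iii), define the blood pressure baseline, and that of any other acutely labile value analysed for change, as the outpatient measurement made at the consultation or within one month of it, under the same conditions as at one year. A value from the index-seizure contact should not serve as this baseline.
3. Record the date and care setting of every baseline value in the electronic case report form.
4. Add a sensitivity analysis that excludes any value from the index-seizure contact.
5. Describe the one-year result as uncontrolled before-after change.

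Do not extend the exclusion to outcome (i): an admission ECG showing atrial fibrillation or a raised HbA1c is a legitimate finding there.

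The cost is a footnote to Table 1, two fields on the form, and a few measurements repeated at a routine visit where a nurse is generally available. Ethics approval and registration are still to come, so the change can be made before any data are collected.
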